*Dynamic mechanical allodynia* (*DMA*)—to test the presence of abnormal stimuli-evoked pain—is assessed with a soft brush (SENSElab, Brush-05, Somedic, Hörby, Sweden) that is swiped 1–2 cm over the skin. This is performed on a single repetition and on a train of three repetitions (wind-up response). At each of the seven body locations (see online supplementary material 1) it is recorded whether the patients feel the sweeping and its pain intensity with a numeric rating scale (NRS) ranging from 0 (no pain) to 100 (most intense pain imaginable) for both the single swipe and the series.^45 46^ The DMA (ratio) is calculated as: DMA=(NRS-3/NRS-1). If NRS-1 is 0, the DMA for that location cannot be calculated and it will be registered as a missing value. The DMA test according to the DFNS protocol has shown to have good test–retest (r=0.87) and interobserver reliability (r=0.79).^44^

*Mechanical pain threshold* (*MPT*)—to test the ability to perceive sharp, pricking or stinging stimuli—is assessed with a set of standardised weighted pinprick stimulators with seven different intensities (the PinPrick Stimulator Set, MRC Systems, Germany) and with a modified method of limits. Starting at the lowest intensity (8 mN), it progressively increases until patients report the stimulus to change from touch to painful (sharp, pricking or stinging). The intensity of the pinprick that produces the first painful stimulus in millinewtons is recorded in each of the seven locations (see online supplementary material 1).^46–49^ The MPT test according to the DFNS protocol has shown to have good test–retest (r=0.80) and interobserver reliability (r=0.80).^44^

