*Wind-up ratio* (*WUR*)—to test the nervous system’s painful stimuli temporal summation or responsiveness to repeated noxious stimuli. Such test is assessed with a suprathreshold pinprick stimulator of 256 mN (the PinPrick Stimulator Set, MRC Systems, Germany), which is applied on a single repetition and on a train of 10 repetitions in an area of 1 cm^2^ with intervals of 1 s (wind-up response). The pain intensity measured with an NRS ranging from 0 (no pain) to 100 (most intense pain imaginable) for both the single repetition and the series is recorded in each of the seven body locations (see online supplementary material 1).^50 51^ The WUR (ratio) is calculated as: WUR=(NRS-10/NRS-1). If NRS-1 is 0, the WUR for that location cannot be calculated and it will be registered as a missing value. The WUR test according to the DFNS protocol has shown to have poor test–retest (r=0.67) and interobserver reliability (r=0.56).^44^

*Mechanical detection threshold* (*MDT*)—to test the ability to detect light touch—is assessed with a standardised set of von Frey filaments (OptiHair2-Set, Marstock Nervtest, Germany) with a modified method of limits.^52 53^ Starting at the intensity of 16 mN, the stimulus application progressively decreases until patients do not report any sensation. The intensity of the filament that is not perceived in millinewtons is recorded in each of the seven body locations (see online supplementary material 1).^54^ The MDT test, according to the DFNS protocol, has shown to have good test–retest (r=0.90) and interobserver reliability (r=0.89).^44^

*Pressure pain threshold* (*PPT*)—to test the ability to perceive pressure pain stimuli on muscles—is assessed with an electronic pressure algometer (Force Ten FDX, Wagner Instruments, USA). With this tool, the pressure in the contact point (1 cm^2^ tip) is progressively but steadily increased until patients report to feel pressure change towards painful (burning, drilling or aching). The intensity in newtons when pressure becomes painful and its pain intensity with an NRS ranging from 0 (no pain) to 100 (most intense pain imaginable) scale is recorded in each of the seven body locations (see online supplementary material 1).^32^ The PPT test according to the DFNS protocol has shown to have good test–retest (r=0.88) and interobserver reliability (r=0.84).^44^

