### Analyses

Data records from the different tests and questionnaires will be collected and merged into one database. The database management will be done by the project team and handled according to the internal regulations of the UMCG. The analyses of the study will be performed with SPSS software version 22.0 (IBM).

Before any analysis, data will be prepared:

Variables need to be calculated: body mass index; DMA, WUR and CPM tests (see the Methods and analyses section, Measurements: CS measurements); PDI, Rand36-PF, PCS, BSI and IEQ questionnaires.HRV: data will be preprocessed to correct for any artefacts that may be present at the beginning or at the end of the recording.QST: the overall value of each sensory test is the mean at the most painful location and the five control locations together, provided that at most two locations are missing.To perform the analyses to respond to objective 3, delta scores are computed (difference in scores between baseline and discharge) for CS, functioning and those confounder variables which are also measured at the same time points as the main measurements.

Proxies of the main measurements were selected to perform analyses. CS variables are: the sum score of CSI part A and the RMSSD for HRV. For QST, no variables are predefined, variables that correlate most strongly with each of the functioning measures will be selected. Functioning variables are: the maximal weight lifted for lifting capacity, the VO_2_max/kg for the maximal aerobic capacity, the daily vector magnitude (VM) counts for PA and the average score of Rand36-PF for reported physical functioning.

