The presence of missing data will be checked. If a variable has more than 10% of missing data cases, its distribution will be further examined. When the distribution of missing data is missing completely at random, analyses with pairwise deletions are planned. If data are not missing completely at random, other suitable solutions will be applied such as multiple imputation.^91^ Regarding the presence of outliers, cases at 3 SD from the mean will be considered as outliers. Their influence will be measured using Cook’s distance and leverage values. When the outliers are not statistically influential and/or there is rationale for the outlier, no further actions are planned. The descriptive statistics of the sample characteristics and main test results will be at this point calculated; numerical variables as mean and SD in normally distributed data and as median and IQR (25–75)) in non-normally distributed data, and categorical variables as counts and percentage of each category level.

*Statistical approach for objective 1: to analyse the association between instruments assessing reference symptoms and signs attributed to CS.* Multiple partial correlation analyses will be performed and corrected for potential confounders. CS measurements will be the main variables and sex and age will be covariates. Additional covariates may enter the partial correlations based on their correlation coefficient with CS instruments and if p<0.01. Results will be reported as correlation coefficients (Pearson’s r and/or Spearman’s rho) and p values, with and without controlling for covariates. The significance level for all analyses is established at 0.01, to account for the potential type I error due to the multitude of partial correlation analyses.
*Statistical approach for objective 2: to analyse whether reference symptoms and signs attributed to CS are associated with functioning measurement outcomes.* First, multiple correlation analyses, followed by multiple regression analyses with data obtained at baseline, will be performed. Each of the main outcomes from functioning measurements will be introduced in the models as dependent variable, CS measurements as independent variables, and sex, age and other demographic characteristics and/or test-related variables as potential confounders and/or moderators.

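### DMA is recorded as missing where the first brush stroke causes no pain, so the normal result becomes absent data; WUR shares the rule, probably with less effect

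*Protocol article*

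**What the plan says.** Under Quantitative sensory testing, DMA is introduced as a test "to test the presence of abnormal stimuli-evoked pain", applied with a soft brush. Pain is rated on a "numeric rating scale (NRS) ranging from 0 (no pain) to 100 (most intense pain imaginable) for both the single swipe and the series". The score at a site is NRS-3 divided by NRS-1, with the rule: "If NRS-1 is 0, the DMA for that location cannot be calculated and it will be registered as a missing value".

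WUR is built the same way, as NRS-10 divided by NRS-1, and has the same rule: "If NRS-1 is 0, the WUR for that location cannot be calculated and it will be registered as a missing value". Its stimulus is different: "Such test is assessed with a suprathreshold pinprick stimulator of 256 mN".

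Under Analyses, the patient's overall value for each sensory test is "the mean at the most painful location and the five control locations together", "provided that at most two locations are missing". The same section says that a variable with more than 10% missing cases has its distribution examined. If the data are missing completely at random, pairwise deletion is planned. If not, "other suitable solutions will be applied such as multiple imputation". Change scores for objective 3 are differences between baseline and discharge.

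**The concern.** On the protocol's own scale, 0 means no pain. For a soft brush that is the expected answer from someone without allodynia, and the test exists to separate such patients from those with allodynia. Recording that answer as missing discards the negative result of the test.

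Four things follow for the DMA variable:

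- Patients who feel no pain from the first stroke at three or more sites have no value, so those who keep one are mainly the more sensitised.
- Patients with one or two such sites are averaged over their painful sites only, so their scores are not comparable with those of patients who have all six.
- A site that goes from 0 to a positive series rating, where pain appears only on repetition, is lost as well.
- A patient who has a DMA value at baseline and becomes pain-free to the first brush stroke at three or more sites by discharge loses the DMA change score.

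The general missing-data rule does not repair this, because nothing is missing: both ratings were observed and only the quotient is undefined.

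**Working it through.** **Inputs.** Six sites enter the overall value (the most painful plus five control sites), and at most two may be missing (Analyses). A site is missing when NRS-1 = 0 (Quantitative sensory testing). The planned sample is 110, which follows from 77 / (1 − 0.30) = 110 (Sample size). The protocol gives no figure for how often NRS-1 is 0, nor for the resulting missingness, so there is no stated figure to reproduce. The share p of sites rated 0 is therefore an assumption and is shown as a range.

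**Step 1: the rule as an event.** The patient's value is missing when X ≥ 3, where X is the number of the six sites with NRS-1 = 0.

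**Step 2: independent sites (assumption).** P(missing) = 1 − [(1−p)^6 + 6p(1−p)^5 + 15p²(1−p)^4].

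- p = 0.2: 1 − (0.2621 + 0.3932 + 0.2458) = 0.099
- p = 0.3: 1 − (0.1176 + 0.3025 + 0.3241) = 0.256
- p = 0.5: 1 − (1 + 6 + 15)/64 = 0.656
- p = 0.8: 1 − (0.0001 + 0.0015 + 0.0154) = 0.983

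Of 110 patients, the expected number keeping a value is 110 × (1 − P): about 99, 82, 38 and 2. The 10% trigger is reached only when p is slightly above 0.20. Below that, the loss is not examined at all.

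**Step 3: correlated sites.** Ratings by one patient are unlikely to be independent. With a common latent normal factor and an assumed inter-site correlation of 0.6, the missing shares at the same four values of p are 20%, 32%, 56% and 88%. Correlation raises the loss when zeros are uncommon and lowers it when they are common.

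**Step 4: the missing-data mechanism.** Whether a site is missing is a deterministic function of its recorded first rating. Missing completely at random would require that first rating to be unrelated to everything under study, yet it measures sensitivity to the brush. Pairwise deletion therefore has no basis. Multiple imputation would supply a number for a quotient that does not exist, in place of two ratings that do.

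**Step 5: direction of selection.** An illustrative simulation used a standard-normal sensitisation trait driving the ratings, with all parameter values assumed. With 13%, 32% and 58% of patients missing, the mean trait was +0.19, +0.41 and +0.73 SD in retained patients and −1.29, −0.89 and −0.53 SD in dropped patients. The direction is what the rule implies. The sizes depend on the assumed values.

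**The case against.** The strongest reply is about reach.

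- **Patients are not removed from the study.** They lose a value on DMA or WUR, two of six sensory tests. The Central Sensitisation Inventory (CSI), heart rate variability (RMSSD) and the other four tests are unaffected. No QST variable is predefined, so DMA may never enter a regression. This stands and limits the consequence.
- **WUR differs.** Its 256 mN pinprick is suprathreshold, so zeros are plausibly rarer. For temporal summation, a ratio to the first stimulus is also a coherent construct. Equal first and series ratings give 1 whatever the pain level because a ratio measures gain rather than severity. This stands: the criticism is mainly of DMA.
- **Objective 3 describes QST improvement as higher pain thresholds.** A reader might infer that the rule destroys the very improvement objective 3 seeks. The Objective section does not support that, since neither DMA nor WUR is a threshold. Only the DMA or WUR change score is lost.
- **Imputation is only an example.** The wording leaves room for another solution, rescoring included. That is fair, but it does not say that these values were observed, and it applies only above the 10% trigger.
- **Sign reversal.** A reader might infer that the rule can reverse the association with functioning. Simulations with an assumed true correlation of −0.40 do not bear this out. With multiplicative summation the ratio kept the correct sign (−0.21 to −0.36). With constant additive summation the wrong sign was largest (+0.23) when only 2% of patients were missing. Any reversal comes from the assumed summation model, not from the missing-value rule.

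**Conclusion.** The point holds as a scoring defect, chiefly for DMA. Followed as written, the protocol turns the normal answer into missing data, keeps the DMA value mainly for more sensitised patients, and averages some patients over painful sites only. This follows from the stated rules and needs no assumption beyond the first rating reflecting sensitivity to the brush.

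The size is not known, because the protocol gives no rate of zero ratings. If 20% to 80% of sites are rated 0, the overall value is missing in 10% to 98% of patients with independent sites, or 20% to 88% with the assumed correlation of 0.6. For WUR the same mechanism applies, probably on a smaller scale. The dropped group is mainly, but not only, the least sensitised, because sites going from 0 to a positive series rating are dropped too. No claim is made about the sign or size of the resulting correlations.

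**What to change.** Before any analysis:

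1. State that NRS-1 = 0 is an observed value and is never deleted or imputed. Reserve missing for ratings that were not taken.
2. Score DMA with a measure valid at zero: the mean brush NRS over the six sites, or presence or absence of brush pain.
3. For WUR, add a summation score defined at zero (NRS-10 minus NRS-1 at each site), or one ratio per patient formed from sums over sites.
4. Report how many sites have NRS-1 = 0, for each test and visit.
5. Keep the published ratios as secondary measures.

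Both raw ratings are already recorded at every site, so this changes scoring only and needs no new data collection. The cost is slightly less direct comparability with published ratios, which reporting them as secondary largely preserves.

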## Introduction

### Background

Twenty per cent of the general population experiences prolonged or recurrent pain for at least 3 months, such pain is then considered to be chronic.^1 2^ Low back pain is the principal cause of years lived with disability and workdays lost in Europe and worldwide,^3^ and its sequelae affect 9% of the global population.^4^ Moreover, although there are several treatment intervention strategies available for patients with chronic low back pain (CLBP), treatment effect sizes have only been moderate.^5^ Such evidence may explain why 40% of the patients are not satisfied with the treatment received.^2^ The economic consequences of chronic pain include direct costs of medical care and pain management treatments, as well as indirect costs of decreased work productivity and sick leave, and of disability and sickness retirement.^2 6^ The indirect costs determine 86%–88% of the total costs produced by patients with CLBP.^7 8^ In particular, in the Netherlands, the costs derived from back pain to Dutch society were 3.5 billion in 2007, corresponding to 0.6% of the gross national product.^8^

In the past decennia, a relevant subsample of patients with chronic pain, including individuals with CLBP, have shown an increased responsiveness to noxious and non-noxious stimuli, described as central sensitisation (CS).^9^ CS is a result of an imbalance in the nociceptive pathways (‘pain pathways’) and supraspinal structures due to an amplified facilitation and/or reduced inhibition.^10–12^ The phenomenon, CS, is manifested by an amplified pain perception regarding its intensity (hyperalgesia and allodynia), duration (aftersensations and temporal summation) and distribution (expansion of the receptive field), as well as a reduced conditioned pain modulation (CPM).^12^ There is currently no gold standard for CS diagnosis. Identifying reference clinical symptoms and signs, however, may indicate the presence of CS: disproportionate pain, diffuse distribution, allodynia and hyperalgesia, hypersensitivity unrelated to mechanical stimulus but rather to environmental sensations (light, temperature, noise or other stressors), maladaptive psychosocial factors and low vagal nerve activity.^13–16^

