### Objective(s)

The objectives of the studies covered by this research protocol are:

To analyse the association between three instruments assessing reference symptoms and signs attributed to CS in patients with CLBP: CSI, QST and HRV.To analyse whether reference symptoms and signs attributed to CS are associated with functioning measurement outcomes in patients with CLBP. Specifically, to analyse the association between the three instruments assessing CS (CSI, QST and HRV) and: lifting capacity, aerobic capacity, PA levels and/or PA distribution or patterns, and patient-reported measurements.To analyse whether changes (between baseline and discharge) in reference symptoms and signs attributed to CS are related to changes in each of the functioning measurement outcomes in patients with CLBP. Specifically, to analyse whether decreases in CS described as: a lower CSI score, an increase in the pain thresholds (QST) and an increase in parasympathetic/vagal tone (HRV) are related to a better functioning described as: an increase in lifting capacity, an increase in aerobic capacity, an increase in PA levels and/or a change in PA distribution or patterns, and better outcome scores in patient-reported measurements.

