*CPM*—to test the nervous system’s descending pain processing. The CPM test methodology selected for this study follows the recommendations of the EFIC meeting (2013).^55^ The pain modulation is assessed by means of PPT tests (test stimuli) in a distant location from patients’ dominant hand (musculus deltoid and musculus quadriceps of the non-dominant side, see online supplementary material 1) before and after immersing the dominant hand in a bucket full with ice and cold water (cold conditioning stimuli). First, PPT measurements at distant locations are made; then, patients immerse the dominant hand in the bucket for as long as they possibly can with a maximal duration of 3 min; finally, PPT measurements are repeated. The PPT results, intensity in newtons and pain intensity with an NRS ranging from 0 (no pain) to 100 (most intense pain imaginable) scale, in both locations and the time the hand is immersed are recorded. The CPM (%) is calculated as: CPM=[(PPTpost–PPTpre)/PPTpre]∗100, where lower values indicate lower alteration on the nociceptive pathways.^33 43^ The CPM test, as the combination of the PPT handheld algometer and cold stimuli, has shown to be one of the most reliable methods with a modest test–retest reliability (ICC=0.49 and coefficient of variation=63.6%).^56^

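### Percent-change CPM is coupled with the starting pressure pain threshold, no covariate for that threshold is named, and the stated direction of the score conflicts with its formula

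*Protocol article*

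**What the plan says.** All references are to the protocol article.

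- **Score.** The Quantitative sensory testing section defines "The CPM (%) is calculated as: CPM=[(PPTpost–PPTpre)/PPTpre]∗100", measured at deltoid and quadriceps on the non-dominant side before and after cold immersion of the dominant hand. It then gives the reading "where lower values indicate lower alteration on the nociceptive pathways".
- **Direction elsewhere.** The Background lists the manifestations of central sensitisation (CS) and ends "as well as a reduced conditioned pain modulation (CPM". The Objective(s) section counts "an increase in the pain thresholds (QST" among the signs of less CS.
- **Reliability.** For PPT: "The PPT test according to the DFNS protocol has shown to have good test–retest (r=0.88". For CPM: "modest test–retest reliability (ICC=0.49 and coefficient of variation=63.6" percent.
- **Use in the models.** "For QST, no variables are predefined, variables that correlate most strongly with each of the functioning measures will be selected". Objective 3 uses simple differences between baseline and discharge.
- **Adjustment.** Sex and age are fixed. Other demographic or test-related variables may enter the models for objectives 2 and 3 if their partial correlation with CS and functioning reaches p≤0.10. For objective 1, extra covariates need p<0.01. PPTpre is not named.
- **Significance.** Correlations are tested at 0.01 and regressions at 0.05.

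**The concern.** PPTpre is both the divisor of the CPM score and the term subtracted in its numerator. PPT is itself one of the study's CS measures. A CPM score that moves with PPTpre carries some pain-threshold signal with the opposite sign. CPM is also the battery's only test of descending inhibition. If functioning depends on PPT, which objective 2 sets out to examine, a real CPM-functioning association may look weaker than it is, or a weak inverse one may appear where none exists.

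A second problem lies in the same sentence. A reader who takes the stated direction literally would interpret the sign of every CPM coefficient the opposite way from a reader who follows the formula and the Background.

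**Working it through.** No figure in the article depends on the CPM score, so there is none to reproduce. The checks below use the formula, the PPT reliability of 0.88 and n=110 (77/0.70, the article's own total). All other inputs are assumptions.

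**1. Arithmetic on the formula.**
- Constant gain of 6 N: 100×6/PPTpre gives 30%, 20%, 15%, 12% and 10% at PPTpre 20, 30, 40, 50 and 60 N. If PPTpre rises from 20 to 30 N between visits and the gain stays at 6 N, CPM falls from 30% to 20%.
- Proportional gain (×1.2): 100×(1.2×PPTpre−PPTpre)/PPTpre = 20% at every PPTpre. A rise from 20 to 30 N changes nothing.

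**2. Coupling through reading error.** On the log scale, ln(PPTpost/PPTpre) = true log gain + e_post − e_pre. Under a proportional gain unrelated to the true threshold, its covariance with ln(observed PPTpre) is −var(e_pre). This is negative whenever PPT is read with error.

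Simulated correlation of CPM% with observed PPTpre (400,000 patients per scenario, one site; assumed mean 40 N, CV 0.3-0.5, mean gain 20%):

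| Gain | No reading error | Reliability 0.88-0.80 |
|---|---|---|
| Constant newtons | -0.25 to -0.33 | -0.33 to -0.41 |
| Proportional | 0.00 | -0.16 to -0.27 |

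**3. Consequence for an association with functioning.** Assumed: PPT mean 40 N, CV 30-40%, reliability 0.88-0.95, conditioning effect 12% (SD 15%), two sites, n=110, sex and age as covariates, and a correlation of 0.3 between functioning and PPT. Test statistic: z = atanh(r)×√(n−3−k), with k covariates.

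- *No true CPM effect, constant-newton gain:* r is about -0.05 to -0.06. With k=2, √105=10.25. At r=-0.05, z=-0.51, which gives a two-sided rejection rate of 8.1% at 0.05 and 2.1% at 0.01. At r=-0.06, z=-0.62, which gives 9.4% and 2.6%. Nearby settings reached -0.08 and 12% (at 0.05).
- *No true CPM effect, proportional gain:* r is about 0.00 and the false-positive rate is 5%.
- *True r of 0.25:* power at alpha 0.05 is as follows.

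| Gain | CPM% alone | CPM% with PPTpre as covariate |
|---|---|---|
| Constant newtons | 21-37% | 59-72% |
| Proportional | 42-64% | 61-74% |

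A repeat run agreed to within four percentage points of power and 0.01 in r. If functioning is unrelated to PPT, adding PPTpre changes power by at most about 3 points. Part of the gain in power comes from removing outcome variance that PPT explains. Because PPTpre is itself read with error, adjustment can leave a residual r of up to about 0.03.

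**4. Changing the score instead.** With a true correlation of 0.30, no functioning-PPT link and reliability 0.88, CPM% gives 0.22 (CV 0.3) or 0.17 (CV 0.5) under a constant-newton gain. The absolute difference gives 0.23 or 0.16, and PPTpost adjusted for PPTpre gives 0.23 or 0.17. A new score therefore gains about 0.01 at most.

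**5. Direction.** By the formula, a positive value means that PPT rose after conditioning, so there was more inhibition. The Background associates CS with reduced CPM, so low values should indicate more CS. The QST section attaches low values to lower alteration.

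**The case against.** The strongest reply is that percent change is the natural score if conditioning raises thresholds proportionally. It is then free of the true threshold, and only reading error couples it with PPTpre. The article attributes the formula to published protocols and calls its sample sizes exploratory. This stands, and it is why CPM% should be kept.

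A reader might infer that a low threshold always raises the CPM score, or that a threshold improving during the programme is recorded as worse inhibition. The article does not support either. Both need a gain that is constant in newtons. Moreover, on the article's stated direction a fall in CPM would count as improvement.

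Other points limit the harm:

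- Under the assumed functioning-PPT link, PPT usually outranks CPM as the selected QST variable. CPM wins in only 3-29% of samples.
- Test-related variables may enter at p≤0.10, and the simple correlations of PPTpre with functioning and with CPM pass that level in most samples. That safeguard is weak where it is needed: among samples in which CPM outranks PPT, PPTpre enters in only about 9-54%.
- Correlations are tested at 0.01, where the excess of false positives is small.
- No simulation was made for delta scores or for the CPM-CSI correlation, so no size can be claimed there.

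On direction, lower alteration might have been meant as less modulation rather than less pathology. In that case the sentence needs to say so. As written it reads as the opposite of the Background.

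**Conclusion.** The point holds in conditional form. Coupling of CPM% with observed PPTpre is certain once PPT is read with error. Coupling with the true threshold depends on a constant-newton gain, on which the article is silent. Dilution of a CPM association and a small spurious inverse correlation are possible only if functioning is related to PPT, and the spurious correlation also needs the constant-newton gain. Under a proportional gain adjustment corrects no such bias and serves precision only.

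The sizes rest on assumed PPT levels, spread, gain and correlations; only the reliability of 0.88 and n=110 come from the article. The effect is modest and bears on the analyses in which CPM is actually used. Adjustment is still worthwhile: PPTpre is already recorded, the power gain is material if the functioning-PPT link exists, and little is lost if it does not.

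The conflict over direction needs no assumption about the gain and is the firmer of the two defects.

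**What to change.** 1. Keep CPM%. Wherever CPM is used in a correlation or regression, also report the result with the mean PPTpre of the two CPM sites as a covariate, named in advance rather than left to the p≤0.10 rule.
2. For objective 3, report as a sensitivity analysis a model with PPTpre at baseline and at discharge next to delta CPM.
3. PPTpost adjusted for PPTpre is a related alternative. It is not equivalent, because the ratio is nonlinear in PPTpre.
4. Reconcile the stated direction of the CPM score with the formula and the Background before any CPM coefficient is interpreted.

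The cost is a sentence or two of text, one degree of freedom (two for objective 3) and an adjusted coefficient that is less comparable with published CPM%. Reporting both results covers that loss. No new data are needed.

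### The stated direction of CPM contradicts its own formula and the Background: lower values mean greater, not lower, alteration

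*Protocol article*

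**What the plan says.** In the Quantitative sensory testing section, PPT is measured at two sites remote from the dominant hand (deltoid and quadriceps of the non-dominant side), "before and after immersing the dominant hand in a bucket full with ice and cold water (cold conditioning stimuli"). The result is expressed as "CPM=[(PPTpost–PPTpre)/PPTpre]∗100", "where lower values indicate lower alteration on the nociceptive pathways". PPT itself is recorded as "The intensity in newtons when pressure becomes painful", so a higher PPT means lower sensitivity.

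The Background describes CS as an imbalance "due to an amplified facilitation and/or reduced inhibition" and lists among its manifestations "as well as a reduced conditioned pain modulation (CPM"). The Objective(s) section counts "an increase in the pain thresholds (QST") as a decrease in CS. It gives no direction for CPM.

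The Analyses section predefines no QST variable. Those correlating most strongly with each functioning measure are to be chosen. It also states that "the overall value of each sensory test is the mean at the most painful location and the five control locations together", as long as no more than two locations are missing.

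**The concern.** CPM is one of six sensory tests that may represent QST in the models, and the sentence beside its formula is the only explicit rule for reading its values. If that rule runs the wrong way, an analyst who follows it will report good inhibition as a sign of CS and failing inhibition as its absence. Objective 3 is directional: it asks whether a decrease in CS goes with better functioning. There, a strengthening of inhibition during rehabilitation would be described as a worsening of CS.

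**Working it through.** **Inputs.** The CPM formula, its stated direction and the meaning of PPT come from the Quantitative sensory testing section. The direction of CPM in CS comes from the Background. The direction of thresholds when CS decreases comes from Objective(s). The plan gives no worked CPM figure to reproduce.

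**Step 1: what the formula does.** CPM = 100 × (PPTpost − PPTpre) / PPTpre. For any PPTpre > 0 the slope in PPTpost is 100 / PPTpre, which is positive. CPM therefore rises strictly with the threshold after conditioning.

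**Step 2: illustration.** The newton values are assumed and are not in the document; PPTpre = 40 N throughout.

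| PPTpost | CPM | Meaning |
|---|---|---|
| 52 N | (52 − 40)/40 × 100 = +30% | threshold rises: inhibition |
| 40 N | (40 − 40)/40 × 100 = 0% | no modulation |
| 32 N | (32 − 40)/40 × 100 = −20% | threshold falls: facilitation |

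By Step 1 the ordering does not depend on the values chosen. The table shows the ordering only and is no guide to judging one patient: the article reports an ICC of 0.49 and a coefficient of variation of 63.6% for this test.

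**Step 3: the two statements side by side.** The Background ties CS to less inhibition or more facilitation, and to reduced CPM. In the table that is the direction from +30% towards −20%, so a lower value means more alteration. The sentence after the formula ranks −20% as least altered and +30% as most altered. Both cannot hold.

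**Step 4: effect on the computed results.** For any variable x and outcome y, r(−x, y) = −r(x, y). Reversing the direction of CPM changes the sign of its correlation or coefficient and nothing else: absolute size, p value and R² are the same. Selection by strongest correlation, taken as absolute size, is also the same. Since CPM is computed from the formula, the reported signs will be right for the formula. Only their verbal reading depends on the sentence.

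**Step 5: the location rule.** The rule averages six locations and allows at most two missing, so it needs at least 6 − 2 = 4. CPM is taken at two sites, so at least 6 − 2 = 4 of the six have no CPM value, whichever locations the supplement (not shown) lists. The general rule and the CPM description do not fit together as worded.

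**The case against.** The strongest defence is that alteration could mean the change that the cold stimulus brings about, so that a low value simply means little modulation. This does not survive the text. The Background uses the word altered for the abnormal state, linked to greater disability, and places the CS imbalance in the nociceptive pathways, the same object as in the disputed sentence. Nor does the reading fit negative values: −20% is a larger change than 0% but a lower number.

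Other parts of the defence stand, and they rule out stronger conclusions that a reader might draw:

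- *That the results themselves would be wrong.* The article gives no recoding, cut-off or composite score for CPM, and the formula is the operative instruction. The statistics are unaffected (Step 4).
- *That patients would be misclassified.* No analysis described in the article classifies patients by CPM.
- *That all three objectives are necessarily affected.* In objectives 2 and 3, CPM matters only if it is selected as the QST proxy or its change score is interpreted. In objective 1 it matters only if it is among the QST variables correlated with CSI or RMSSD.
- *That no patient would receive a CPM value.* This needs a very literal reading of the location rule. A site never scheduled for CPM is not missing in the usual sense, the Analyses section lists CPM among the variables to be calculated, and an analyst would most likely average its two sites. This is a wording conflict only.

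**Conclusion.** The direction sentence is wrong as written. It contradicts the formula it accompanies, read with the article's own account of CS, and the contradiction can be shown from the document alone. It is more than a clerical slip, because it is the only explicit rule for interpreting CPM and following it would reverse the conclusion wherever CPM is interpreted. The damage is confined to interpretation: coefficient sizes, p values, explained variance, sample size and proxy selection are untouched, and the reach depends on whether CPM enters the reported analyses. The conclusion assumes only that PPTpre is positive and that alteration has the meaning it has elsewhere in the article. The two-site point is secondary and needs only clarification.

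**What to change.** Before analysis:

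1. Replace the direction clause with: *where lower (or negative) values indicate less efficient pain inhibition, i.e. greater alteration*. Reversing the sign of the formula and keeping the clause would also remove the contradiction, but then a reduced CPM in the Background's sense would be a higher number. Correcting the clause is simpler.
2. In objective 3, state that a decrease in CS corresponds to an increase in CPM.
3. In the Analyses section, state that the overall CPM value is the mean of its own two sites and that the six-location rule does not apply to it.

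The cost is a few words, with no new data, no change to the sample size and no change to the models.
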